## Abstract

**Background:**

A plethora of observational evidence exists concerning the impact of management and leadership on workforce, work environment, and care quality. Yet, no randomised controlled trial has been conducted to test the effectiveness of leadership and management interventions in aged care. An innovative aged care clinical leadership program (Clinical Leadership in Aged Care − CLiAC) was developed to improve managers’ leadership capacities to support the delivery of quality care in Australia. This paper describes the study design of the cluster randomised controlled trial testing the effectiveness of the program.

**Methods:**

Twenty-four residential and community aged care sites were recruited as managers at each site agreed in writing to participate in the study and ensure that leaders allocated to the control arm would not be offered the intervention program. Sites undergoing major managerial or structural changes were excluded. The 24 sites were randomly allocated to receive the CLiAC program (intervention) or usual care (control), stratified by type (residential vs. community, six each for each arm). Treatment allocation was masked to assessors and staff of all participating sites. The objective is to establish the effectiveness of the CLiAC program in improving work environment, workforce retention, as well as care safety and quality, when compared to usual care. The primary outcomes are measures of work environment, care quality and safety, and staff turnover rates. Secondary outcomes include manager leadership capacity, staff absenteeism, intention to leave, stress levels, and job satisfaction. Differences between intervention and control groups will be analysed by researchers blinded to treatment allocation using linear regression of individual results adjusted for stratification and clustering by site (primary analysis), and additionally for baseline values and potential confounders (secondary analysis). Outcomes measured at the site level will be compared by cluster-level analysis. The overall costs and benefits of the program will also be assessed.

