The CLiAC is a structured manager education and support program that starts with four modules covering core leadership topics delivered in eight full-day workshops. Action learning techniques, 360-degree feedback, case scenarios, one-on-one interactions with a program facilitator, and individual practice improvement projects are included in the 12-month CLiAC program, which is facilitated in the participant’s workplace. The program is designed in such a way that it is congruent with, and incorporated into, the governing organisation’s philosophy, policies, leadership and strategic directions on the grounds that the program delivery requires the organisation’s support, and also that the full potential of effective leadership of middle managers can only be realised when those organisational elements align with the individual’s leadership efforts [23,24].

The CLiAC program is delivered by a facilitator employed specifically for the program by the collaborating organisation, to ensure continuity of the program beyond the study lifetime. The research team and the collaborating organisation worked together to develop the job description for the facilitator. Emphasis was on: first, authenticity of the person who understands the aged care setting and has substantial experience and knowledge in leadership and management; and second, the person’s capacity to be ‘a facilitator and mentor’ rather than ‘an educator.’ The facilitator’s role is to support participants throughout the program via individual meetings and/or teleconferences every four to six weeks, convene group discussions during workshops, provide coaching and participate in peer support meetings. Program participants receive a set of learning resources that include templates for team building activities, developing team-based action plans, providing education sessions, and undertaking the clinical care improvement project.

To enable commitment to the intervention, the facilitator is mentored and supported by an expert education consultant who played the key role in developing the ACLQF and the CLiAC. Weekly contact is maintained throughout the intervention. The facilitator keeps a diary of relevant activities (all formal and informal communication and activity details involving the facilitator and the participants of the CLiAC). The information, with personal details removed, is then sent to the research team on a monthly basis.

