### Hypotheses

The trial consists of two arms: intervention and control. Managers at the intervention sites agreed to receive the CLiAC program. At the control sites, managers agreed to provide usual care services during the study. The primary hypotheses are that, compared to the control sites, managers and staff at the intervention sites will report an enhanced work environment for staff (H_1_); and improved care quality and safety for care recipients (H_2_); and will have reduced staff turnover rates (H_3_). Secondary hypotheses include that, compared to the control sites, the intervention sites will report: reduced staff absenteeism (H_4_), improved staff ‘intention to stay’ and decreased ‘intention to leave’ (H_5_), reduced stress levels in aged care staff (H_6_), increased job satisfaction for aged care staff (H_7_), reduced costs of retaining and recruiting staff (H_8_), and improved managers’ knowledge and skills in leadership and management (H_9_).

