### Participants and sampling frame

Participants are both the care staff and the middle managers of the targeted residential and community aged care services. The sample size calculation was based on the primary outcome, participants’ perceived work environment: the subscales of the Work Environment Scale-R (WES-R) [26]. The study has 80% power to detect a difference of 0.49 standard deviations between groups as significant at the 5% level. This assumes that at least 20 clusters (sites) each with a minimum of 30 participants will complete the study, and that the intra-cluster correlation coefficient (ICC) is 0.26 (average estimate from a recent nursing home staff training intervention carried out in England and Wales) [27], giving a design effect of 8.54. The detectable difference is consistent with the WES-R [26] test developer’s recommendation that half a standard deviation represents a meaningful change on the instrument ([name], personal communication, Dec. 4, 2008). Consequently, the study will be able to detect a meaningful difference between the trial groups, and it is practical and feasible in terms of study design and data collection.

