### Randomisation and blinding

After recruitment of the 24 sites to the study and collection of baseline (Time 1) data from all sites, the sites were allocated to either the intervention or control arm by a biostatistician ([name]) who was not involved in recruitment, data collection, or contact with the sites. Sites were stratified by type of aged care (RACF vs. CACS). Within each stratum, restricted randomisation was used to balance the groups by: size of the service (number of clients), span of control (care staff to middle management ratio), and geographical location (rural vs. urban) [28]. Location is balanced exactly, while for size and span of control the means of the two groups are allowed to differ by no more than 10% in relative terms (*i.e*., ratio of means between 0.9 and 1.1). Allocation was thus fully concealed. The sites were notified by email and completed a written agreement to abide by the random allocation. Also, in an attempt to reduce bias associated with staff becoming aware of managers attending the CLiAC program, participating managers signed forms agreeing not to discuss with their work teams and staff any group specific activities or training that have occurred, and agreed to maintain blinding until the end of data collection. The members of the research team responsible for data entry and analysis will remain blind until completion of the main analysis.

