### Collation of data on quality indicators (H_2_ – Care quality and safety)

Quality indicator data included information on the number of unplanned hospital admissions, falls with injury, unintentional weight loss greater than two kilograms, new pressure areas, and new urinary tract infections [34]. These indicators were chosen for their appropriateness and relevance to both community and residential care settings and the fact that they were already part of the regular data collection of the collaborating organisation. Table 3 provides details of the clinical indicators. The data was collected monthly throughout the study (for a total period of two years) using a standardised spreadsheet. For each quality variable, a common set of criteria was detailed and provided to each site along with the spreadsheet. Senior management at all study sites collated the quality indicator data on the last day of each month and sent the spreadsheet to the research team.

**Table 3 T3:** Clinical indicators

**Indicators**	**Definition and criteria**
**Fall with injury**	A fall is an event that results in a person coming to rest inadvertently on the ground or floor or other lower level. If a client is found on the floor or ground, it should be assumed that they have fallen (unless they are cognitively unimpaired and indicate that they put themselves there on purpose). Signs of injury may include fracture, bruises, skin tears, sprains, lacerations, reddened areas or aggravation of pre-existing complaints such as back pain.
**New urinary track infection**	If the resident does not have an indwelling catheter, they must have at least three of the following signs or symptoms:
	1. Fever (greater than 38°C) or chills;
	2. New or increased burning pain on urination, frequency or urgency;
	3. New flank or suprapubic pain or tenderness;
	4. Change in the character of urine;
	5. Worsening of mental or functional status;
	6. New or increased incontinence.
	If the resident has an indwelling catheter, they must have at least two of the following signs or symptoms:
	1. Fever (greater than 38°C) or chills;
	2. New flank or suprapubic pain or tenderness;
	3. Change in the character of urine;
	4. Worsening of mental or functional status.

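### The abstract's masking claim does not hold for managers, who answer the primary survey and, at senior level, collate the clinical indicators; a care-staff-only analysis should stand beside the primary one

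*Protocol article*

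**What the plan says.** **The masking claim.** The abstract's Methods paragraph says: "Treatment allocation was masked to assessors and staff of all participating sites".

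**Who knew the allocation.** Under Hypotheses: "Managers at the intervention sites agreed to receive the CLiAC program". Under Randomisation and blinding: "The sites were notified by email and completed a written agreement to abide by the random allocation". The same section says that "participating managers signed forms agreeing not to discuss with their work teams and staff any group specific activities or training that have occurred". It limits blinding of the research team to data handling: "The members of the research team responsible for data entry and analysis will remain blind until completion of the main analysis".

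**Who supplies primary data.** Under Participants and sampling frame: "Participants are both the care staff and the middle managers of the targeted residential and community aged care services". H1 and H2 are worded as what managers and staff will report, and both groups fill in the survey containing the WES-R (H1) and the ADQ and P-CAT (H2). For the clinical indicators, also H2: "Senior management at all study sites collated the quality indicator data on the last day of each month".

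**The analysis.** The Data analysis plan describes a linear regression at Time 3, adjusted for service type and for clustering by site. It gives no job-role term and no exclusion of managers. Role is also absent from the listed individual-level confounders for the secondary analyses.

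**The concern.** The outcomes at issue are self-rated scales and locally collated event counts. Both are open to influence from knowing the arm. A manager who has spent a year in a leadership programme may rate the workplace or its care differently without any change for care staff or clients. A senior manager who knows the site is an intervention site may apply the indicator criteria more or less closely. A reader who trusts the abstract would assume that masking protects against both.

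If manager and care-staff answers are analysed together, a reporting shift confined to managers carries into the primary contrast in proportion to their share of respondents. That share is raised because, at the time of writing, 81% of manager surveys but only 41% of staff surveys had been returned (Trial status).

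**Working it through.** **Step 1: compare the claim with the body of the article.**

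- *Middle managers, intervention arm.* They attend eight workshop days within a 12-month programme (The CLiAC intervention) and sign non-disclosure forms. They cannot be masked.
- *Managers, control arm.* They agreed to provide usual care, and their sites were notified and signed to abide by the allocation.
- *Senior managers.* The article does not say outright that the collators knew the arm. Notification of sites implies it. So does the disqualification rule under Recruitment of targeted aged care sites, which turns on whether a replacement senior manager at an intervention site supports the intervention.
- *Care staff.* Masking was attempted through the managers' forms.
- *Data entry and analysis.* Blinded, but these people do not generate the outcomes.

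Even if staff in the abstract means care staff only, those who collate the H2 indicators act as assessors of that outcome, and nothing in the text masks them.

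**Step 2: how a manager-only shift carries through.** The documents give neither the number of managers nor the size of any shift, so both are assumed. With m the managers' share of those invited, and equal shares in both arms:

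share of respondents r = 0.81m / (0.81m + 0.41(1 − m))

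pooled shift = r × manager-only shift

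For m = 10%: r = 0.081 / (0.081 + 0.369) = 18.0%.

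| m (assumed) | r | Pooled shift (SD) for a manager shift of 0.25 / 0.5 / 1.0 SD | 0.5 SD case relative to 0.49 SD |
|---|---|---|---|
| 5% | 9.4% | 0.024 / 0.047 / 0.094 | 10% |
| 10% | 18.0% | 0.045 / 0.090 / 0.180 | 18% |
| 20% | 33.1% | 0.083 / 0.165 / 0.331 | 34% |

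**Step 3: effect on the error rate.** The article's design effect reproduces: 1 + 29 × 0.26 = 8.54. With 20 sites in total and 30 respondents each, there are 300 per arm, or 300 / 8.54 = 35.13 effective per arm. The standard error is √(2 / 35.13) = 0.239 SD. With no true effect, a pooled shift of 0.05, 0.10 or 0.20 SD raises a two-sided 5% error rate to 5.5%, 7.0% or 13.4%.

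**Step 4: precision of a care-staff-only analysis.** The detectable difference at 80% power, two-sided 5%, is 2.80 × √(2 / effective n per arm).

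- 30 per site: 0.668 SD.
- 27 per site (10% removed): design effect 1 + 26 × 0.26 = 7.76; 270 / 7.76 = 34.8; 0.672 SD.
- 20 per site (one third removed): design effect 1 + 19 × 0.26 = 5.94; 200 / 5.94 = 33.7; 0.683 SD.

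Clustering dominates, so removing managers costs little. The 0.668 SD differs from the article's 0.49 SD. That is a separate sample-size question, which neither supports nor weakens this point; only the change between rows matters here.

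**The case against.** **The wording may be narrower than it looks.** The article usually separates managers from staff, so the abstract may claim masking of care staff only, and the body discloses the arrangement openly. This stands for the word staff. It does not rescue assessors as applied to the clinical indicators.

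**Pooling is not stated.** A reader might infer that manager and care-staff scores are certainly combined. The text does not say so. It follows from the participant definition, the wording of H1 and H2, and a single regression of individual results. The economic section refers to scales assessed by staff, and a full analysis plan could separate roles. The inference is strongest for the WES-R. For the ADQ and P-CAT it is weaker, because the plan names H2 among outcomes measured at cluster level.

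**Senior managers collate.** It is tempting to say that they classify events. The article says only that they collate, with common criteria and a standard spreadsheet, data that the organisation already collected. That reduces the scope for bias but does not mask the collators.

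**Care staff may have remained unaware.** A reader might infer unmasking from the programme's components ("Action learning techniques, 360-degree feedback, case scenarios, one-on-one interactions with a program facilitator"). The article does not say who gives the feedback, so this is conjecture.

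**Restricting the primary analysis to care staff would change the hypothesis.** H1 and H2 name managers as well as staff, and all surveys were already in. This objection stands, and the fix respects it.

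**Conclusion.** The point holds in a limited form. The masking statement does not hold for managers' survey answers or for the clinical indicators, and the primary regression as described does nothing to separate masked from unmasked respondents. The consequence is a risk of reporting bias, not a demonstrated bias. Its direction is unknown: trained managers might rate higher, while closer vigilance might raise recorded events.

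The size cannot be derived from the documents. Under an assumed 0.5 SD manager-only shift and a 5% to 20% manager share of those invited, it is 0.05 to 0.17 SD, which is modest at the low end and about a third of the planned difference at the high end. The calculation assumes that the return rates, given as averages so far, apply equally in both arms.

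For the indicators, which are analysed at cluster level, the issue is unmasked ascertainment rather than pooling, and filtering survey respondents cannot address it. Staff turnover comes from the organisation's human resource records and is outside this point.

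**What to change.** 1. Replace the abstract sentence with: *Care staff were not told the allocation and analysts were blinded; managers, including the senior managers who collate the clinical indicators, were not masked.*
2. Interpret the clinical indicators as collected without masking.
3. Before unblinding, specify a care-staff-only analysis of WES-R, ADQ and P-CAT in both arms, reported alongside the primary analysis, with manager results shown separately.

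The survey already records current job role, so no new data are needed. According to Trial status, analysis had not begun when the article was written, so the addition could be fixed without knowledge of results. The cost is one sentence and one additional analysis on a somewhat smaller sample. The primary population named in H1 and H2 need not change.

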**Discussion:**

The outcomes of the trial have the potential to inform actions to enhance leadership and management capabilities of the aged care workforce, address pressing issues about workforce shortages, and increase the quality of aged care services.

**Trial registration:**

Australian New Zealand Clinical Trials Registry (ACTRN12611001070921)

## Background

Most older people in their sixties and seventies actively contribute to the social and economic fabric of society, and maintain reasonably healthy, independent lifestyles without assistance in their personal and everyday activities [1]. However, extended longevity is accompanied by increasing health issues, in particular chronic diseases and multi-morbidity, and consequently there is a growing need for aged care services, both in residential and community settings [2-5]. The rising expectations of service standards among older people and their families further create greater demands on health and aged care services, managers and staff. Along with the increasing care needs of an ageing population, there is a continued demand for therapeutic nursing care to be provided or supervised by a registered nurse. However, the ability of aged care services to provide high-quality care to this population is often challenged due to a number of aged care workforce issues, including inadequate financial and human resources and skill mix, often accompanied by difficulties in recruiting and retaining qualified nurses with the necessary skills [4,6].

Over time, these issues have led to a substantial change in the aged care workforce profile, where aged care services are now increasingly staffed by care workers (non-licenced workforce) who have limited knowledge or skills in aged or chronic care [7,8]. Changes in the workforce profile have also resulted in a decrease in numbers of managerial staff available to supervise and provide leadership within the sector [9]. Staff shortages, low levels of staff education, low levels of skills in the speciality area, and reduced career prospects for aged care staff compared with their acute and community counterparts, all combine to influence the quality of care services provided in the aged care sector. Such trends are not limited to Australia [10,11].

There is a growing recognition of the need to place a greater emphasis on the quality of individual and organisational leadership capabilities in aged care [12], given their impacts on care quality and safety and staff outcomes [13,14]. Creating a supportive work environment is one of the key strategies to improve staff retention in a sector marginalised by ageist social attitudes [8]. A supportive work environment promotes a strong service mission where staff have ‘adequate supervision, access to professional and emotional support, the establishment of systems that provide feedback to staff (such as regular staff appraisal), and the presence of strong professional leadership’ [8], p.55. National and international evidence point to the significant influence of leadership and management skills on staff turnover, retention and job satisfaction [8,15,16], quality of care, patient outcomes and organisational efficiency [17,18]. The high costs of poor leadership and unhealthy work environments are shown in staff dissatisfaction, absenteeism, and high turnover [19]. Poor leadership has been linked to high staff turnover, but it is yet to be established that poor leadership and high staff turnover relate synergistically to reduce care quality and increase service costs, such as the additional costs of treating urinary tract infections and pressure sores in aged care residents [19-21].

The purpose of this manuscript is to describe the study design and methods of the first cluster randomised controlled trial of an aged care specific leadership program (CLINICAL Leadership in Aged Care – CLiAC). The CLiAC program was developed in recognition of the issues outlined above and the need to focus on the quality of clinical, individual and organisational leadership and management capabilities in both residential and community aged care services in Australia. The aim of the study is to determine the effectiveness of a clinical and managerial leadership program in aged care in improving work environment, workforce retention, as well as care safety and quality, which have not been previously researched in the aged care sector.

### The CLiAC intervention

Leadership is a broad term with a diverse range of applications depending on the position and role of leaders/managers. In aged care services, the middle manager’s role involves ensuring that care quality and safety occur through timely and detailed assessment of care recipients’ health, development of treatment plans, and supervision of nursing staff and care workers [22]. These role responsibilities suggest that leadership capabilities optimise the middle manager’s use of positional authority in leading others to achieve high-quality service outcomes. Yet little evidence exists about the best ways to enable middle managers of aged care services to develop the leadership and management skills that are critical to the effective delivery of high-quality care [23].

The CLiAC aims to achieve safe, high-quality person-centred and evidence-based care by assisting middle managers to develop effective team relationships and person/client-centred leadership strategies that enable them to deal with the day-to-day realities of care service. The Aged care Clinical Leadership Qualities Framework (ACLQF), which was developed from a comprehensive narrative synthesis of leadership and management literature [11] and validated as part of a larger action research project (manuscript under review), underpins the CLiAC program. The findings of the review [11] and the Clinical Excellence Commission Clinical Leadership (CECCL) program [22] further provided the guiding principles of the CLiAC and its implementations, which include that: a leadership program must be incorporated as part of approaches to organisational development and with a strong commitment from the organisation; middle managers are the main target group, but training middle managers should be inclusive of other management levels (*i.e*., senior and frontline managers); and the implementation of the leadership program should occur for 10 to 12 months in which the learning is embedded in the participants’ day-to-day activities.

The CLiAC is a structured manager education and support program that starts with four modules covering core leadership topics delivered in eight full-day workshops. Action learning techniques, 360-degree feedback, case scenarios, one-on-one interactions with a program facilitator, and individual practice improvement projects are included in the 12-month CLiAC program, which is facilitated in the participant’s workplace. The program is designed in such a way that it is congruent with, and incorporated into, the governing organisation’s philosophy, policies, leadership and strategic directions on the grounds that the program delivery requires the organisation’s support, and also that the full potential of effective leadership of middle managers can only be realised when those organisational elements align with the individual’s leadership efforts [23,24].

The CLiAC program is delivered by a facilitator employed specifically for the program by the collaborating organisation, to ensure continuity of the program beyond the study lifetime. The research team and the collaborating organisation worked together to develop the job description for the facilitator. Emphasis was on: first, authenticity of the person who understands the aged care setting and has substantial experience and knowledge in leadership and management; and second, the person’s capacity to be ‘a facilitator and mentor’ rather than ‘an educator.’ The facilitator’s role is to support participants throughout the program via individual meetings and/or teleconferences every four to six weeks, convene group discussions during workshops, provide coaching and participate in peer support meetings. Program participants receive a set of learning resources that include templates for team building activities, developing team-based action plans, providing education sessions, and undertaking the clinical care improvement project.

To enable commitment to the intervention, the facilitator is mentored and supported by an expert education consultant who played the key role in developing the ACLQF and the CLiAC. Weekly contact is maintained throughout the intervention. The facilitator keeps a diary of relevant activities (all formal and informal communication and activity details involving the facilitator and the participants of the CLiAC). The information, with personal details removed, is then sent to the research team on a monthly basis.

